### **10.3 Missing data**

The relevant researcher will contact the premature infant's guardian by telephone or check electronic medical records to supplement missing baseline and follow-up data. If no reply is received from the guardian or missing data cannot be supplied, the missing data will be processed using different methods based on the mechanism of the missing data. For example, mean value imputation and last observation carried forward will be used to supplement the data. Furthermore, we will conduct a sensitivity analysis to evaluate the robustness of trial results: When we analyze primary outcomes, we will conduct a comparative analysis of complete (ignoring the missing data) and incomplete (no missing data) cases.

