## **11. Sample size and statistical power estimation**

The sample size estimate is based on our pilot study; the time of complete meconium evacuation was 1.4 days, 1.2 days, and 1.2 days earlier in the breast milk enema group than in the saline enema group at  $23 \text{ w} \leq \text{gestational age} < 28 \text{ w}$ ,  $28 \text{ w} \leq$

gestational age < 29 w, and 29 w  $\leq$  gestational age < 30 w, respectively. Given that  $\alpha = 0.05$ ,  $\beta = 0.2$ , standard deviation (SD) = 2, sampling ratio = 1 and taking a 20% drop rate into account, the required total sample size is 78, 108, and 108 premature infants in each gestational age, respectively. A website was used to calculate the sample size (<http://powerandsamplesize.com/Calculators/>).

| Gestational age               | Difference | $\alpha$ | $\beta$ | SD | Sample size | Loss of follow-up | Final sample size |
|-------------------------------|------------|----------|---------|----|-------------|-------------------|-------------------|
| 23W $\leq$ Gastinal age < 28W | 1.4d       | 0.05     | 0.2     | 2  | 64          | 20%               | 78                |
| 28W $\leq$ Gastinal age < 29W | 1.2d       | 0.05     | 0.2     | 2  | 88          | 20%               | 108               |
| 29W $\leq$ Gastinal age < 30W | 1.2d       | 0.05     | 0.2     | 2  | 88          | 20%               | 108               |

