### **14.6 Statistical software**

A two-sided  $P < 0.05$  will be considered statistically significant. All analysis will be performed in SAS version 9.2 (SAS Institute Inc., Cary, NC, USA) and SPSS version 22.0 (IBM Inc., Chicago, IL, USA) software. Interim analyses are not planned.

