## 15. Discussion

Due to the large number of premature infants being born worldwide, countries are facing an enormous medical burden. Feeding is a significant challenge for premature infants and establishing full enteral feeding is an important goal in their care. Earlier full enteral feeding is associated with fewer failures of postpartum growth. Unfortunately, any delay in meconium excretion is related to a delay in transition to full enteral feeding. Compared with term infants, many premature infants pass the first meconium only after considerable delay. Times for the evacuation of the first and last meconium is critical for gastrointestinal function and feeding tolerance. If meconium evacuation can be expedited through the use of an effective enema, this may lead to a faster transition to full enteral feeding and a decreased reliance on intravenous nutrition. However, the available evidence is inconclusive. In contrast to other enemas, the amount of magnesium salts in breast milk is high and relatively stable, which can promote gastrointestinal peristalsis and help meconium evacuation[21,22]. In addition, breast milk can reduce the risk of enterovirus infection and balance the intestinal flora of premature infants[23,24]. Therefore, the trial will collect all participants' data to determine whether this trial has potential clinical significance and can provide reliable evidence for clinical intervention. The results may yield a new, safe, inexpensive, and easy-to-use intervention to effectively evacuate meconium in preterm infants.

To the best of our knowledge, the major strength of this randomized controlled trial is to evaluate, for the first time, the effectiveness of a breast milk enema in promoting complete meconium evacuation and reach full enteral feeding among preterm and extremely preterm infants. Consequently, the results will provide critical information regarding a new enema to effectively evacuate meconium in preterm infants.

The study protocol has several limitations. First, some infants achieving complete meconium evacuation may withdraw before observing the time to reach full enteral feeding. We will further analyze and design a more comprehensive investigation

482 based on this study. Second, this trial is a single-center clinical trial. Therefore, the  
483 representativeness of the participants is limited to some extent. Finally, some mothers  
484 may be unable to produce enough breast milk in early postpartum, which may slow  

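### The robustness check in section 10.3 (complete cases against imputed data) does not vary the unobserved times towards slower lost infants, so agreement is no evidence against bias from informative loss

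*Protocol*

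**What the plan says.** Protocol section 10.3 first tries to retrieve missing data from guardians and medical records. What remains is handled by methods that depend on the missing-data mechanism, and two are given as examples: "mean value imputation and last observation carried forward will be used to supplement the data". It does not say whether the mean is that of the infant's own arm or of all infants. The robustness of the primary results is then to be judged as follows: "we will conduct a comparative analysis of complete (ignoring the missing data) and incomplete (no missing data) cases". The labels are confusing, since the incomplete cases are said to have no missing data. The sensible reading is complete cases on one side and the filled-in data set on the other.

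Three other places matter:

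- Section 11 sizes the trial "taking a 20% drop rate into account".
- Section 15 expects that "some infants achieving complete meconium evacuation may withdraw before observing the time to reach full enteral feeding", which is loss before the second primary outcome.
- Sections 14.1 and 14.2 plan intention-to-treat and per-protocol analyses, t-test or Mann-Whitney comparisons, a Hodges-Lehmann difference, and Kaplan-Meier and log-rank analyses.

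**The concern.** A sensitivity analysis for missing data should change the assumption about what was not seen. Here both sides rest on the same observed event times; LOCF adds only an early stopping point. The comparison never asks whether the result survives if infants lost from the breast-milk arm were slower to clear meconium or to reach full feeds.

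That is the direction that matters. Treatment is open-label (section 6), and an infant who leaves before full enteral feeding may be one who is doing badly. If such losses fall mainly in the breast-milk arm, the complete-case difference is biased in favour of breast milk. The filled-in analysis would then usually agree with it, and that agreement could be reported as robustness.

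**Working it through.** **The plan's own figure.** Inputs from section 11: differences "was 1.4 days, 1.2 days, and 1.2 days earlier in the breast milk enema group than in the saline enema group", then "standard deviation (SD) = 2, sampling ratio = 1 and taking a 20% drop rate into account". Section 14.6 gives the level: "A two-sided $P < 0.05$ will be considered statistically significant". With n per arm = 2(1.96 + 0.84)² × 2² / δ²:

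- δ = 1.4 gives 32.04 per arm, or 64 in total.
- δ = 1.2 gives 43.60, rounded to 44 per arm, or 88 in total.

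Both match the table. For 20% loss, 64/0.8 = 80 and 64 × 1.2 = 76.8 (plan: 78); 88/0.8 = 110 and 88 × 1.2 = 105.6 (plan: 108). The sizes reproduce closely enough for this point. Per arm they are 39, 54 and 54, or 147 overall. With 20% lost, about 31, 43 and 118 per arm are observed.

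**Arm-mean imputation, pooled t-test.** Let m of N per arm be observed. Filling in the arm mean leaves the difference and the within-arm sum of squares unchanged, while the variance divisor and the sample size both rise. So t is multiplied by √[((2N−2)/(2m−2)) × (N/m)]:

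| N per arm | m observed | Factor on t | Complete-case p that becomes 0.05 |
|---|---|---|---|
| 39 | 31 | 1.26 | 0.120 |
| 54 | 43 | 1.26 | 0.119 |
| 147 | 118 | 1.25 | 0.116 |

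The factor always exceeds 1 and the critical value falls slightly, so no positive t-test can be overturned. By the same arithmetic, random loss with no true effect gives about 12% rejections instead of 5%.

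Example at the planned effect, N = 39 and m = 31:

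- Complete cases: t = 1.4/(2√(2/31)) = 2.76, p = 0.0077.
- Arm mean: sum of squares 60 × 4 = 240, variance 240/76 = 3.158, SE = √(3.158 × 2/39) = 0.402, t = 3.48, p = 0.0008.

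**Overall-mean imputation, same example.** The difference shrinks to 1.4 × 31/39 = 1.113. The sum of squares becomes 240 + 2 × (31 × 8/39) × 0.7² = 246.2. SE = √((246.2/76) × 2/39) = 0.408, t = 2.73, p = 0.0079. The difference and SE shrink together, so the verdict barely moves.

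**Simulation at the planned effects** (2,000 trials per setting, 39 or 54 per arm, normal or lognormal times, SD 2). The table gives the share of positive complete-case results that were overturned:

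| Test and imputation | Loss 20%/20% | Loss 35%/5% |
|---|---|---|
| t-test, arm mean | 0 | 0 |
| t-test, overall mean | 0 | about 1-2% |
| Mann-Whitney, arm mean | 0-0.3% | 0-2.6% |
| Mann-Whitney, overall mean | about 2-5% | about 8-16% |

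In the other direction, about 40-50% of negative t-tests became positive after arm-mean imputation.

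**Informative loss, no true overall effect.** The protocol gives no loss mechanism, so these are assumptions. Suppose retained breast-milk infants are d days faster than control, and the lost 20% are d × 0.8/0.2 = 4d days slower, so that the full arm means are equal. Lost controls behave like retained ones. The complete-case t-test has SE = 2√(2/m) and is falsely significant in:

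| d (lost infants slower by) | 39 per arm, SE 0.508 | 54 per arm, SE 0.431 | 147 per arm, SE 0.260 |
|---|---|---|---|
| 0.4 d (1.6 d) | 12% | 15% | 33% |
| 0.6 d (2.4 d) | 21% | 28% | 63% |
| 0.8 d (3.2 d) | 34% | 45% | 86% |

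Mean imputation, arm or overall, confirmed all of these false positives by t-test in simulation. Under a second assumed mechanism (slowest 20% lost from the breast-milk arm, 39 per arm, normal times), complete cases were falsely significant in 34% and arm-mean data in 48%; none was overturned.

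**LOCF.** Assume that a lost infant is assigned the withdrawal time, that times have mean 7 d and SD 2 d, and that withdrawal is uniform between birth and the true event. In the first informative-loss scenario about 80% of the false positives then became non-significant (77-86% across runs). The disagreement arises because lost infants in both arms receive times earlier than their true ones, which adds noise and moves the estimate. Slower lost infants are never tried.

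**The case against.** The strongest reply is that a reader might infer a check that can never fail, and the protocol does not support that. The text never says arm mean; it names mean imputation and LOCF only as examples and lets the method depend on the mechanism. Under LOCF the two analyses often disagree. The always-confirmed result is exact for the pooled t-test only, whereas section 14.2 takes its difference and interval from Mann-Whitney and Hodges-Lehmann methods. Negative results can flip, which would show as disagreement. No rule is stated that two significant results mean robust. All of this stands and limits the claim.

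The size is also open to challenge. The false-positive rates come from complete-case bias that was put in by assumption, and 20% is a planning allowance. Daily follow-up (section 12.8), data retrieval (section 10.3) and consent to use data after withdrawal (section 4.4) should reduce loss. This stands too: the rates illustrate and do not predict.

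A reader might also infer that the fault is the lack of a missing-not-at-random analysis. That would not be a finding, because a separate analysis plan may contain one. The point is narrower: the protocol names a specific comparison as its evaluation of robustness, and that comparison does not do this job. The per-protocol analysis and the Kaplan-Meier and log-rank analyses do not fill the gap. The per-protocol set does not vary unobserved times, and the log-rank test assumes non-informative censoring.

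**Conclusion.** The point holds in limited form. Agreement between complete cases and single-imputed data is not evidence of robustness to informative loss, because neither side lets lost infants be slower. The confirmation of positive t-tests under arm means is algebra and needs no loss mechanism. Under overall means with equal loss it is essentially complete; for Mann-Whitney it is usual but not certain. Disagreement under LOCF reflects artificially early times. How often a false positive would pass depends on the assumed mechanism and on which sample size applies, since section 11 powers each gestational-age stratum separately. The change is worth making but does not invalidate the primary analysis.

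**What to change.** In section 10.3:

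1. Keep the complete-case result as description only, and correct the garbled labels.
2. Replace the complete-versus-imputed comparison as the robustness check with a delta (tipping-point) analysis of each primary outcome. Lengthen the times of infants lost before the event by increasing numbers of days, first in the breast-milk arm only and then in both arms, and report the shift at which P < 0.05 is lost.
3. State the starting values to which the shift is added. These should not be single arm means, or the understated standard error shown above carries over.

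Report the tipping shift as a number for readers to judge. The cost is a rewritten passage in section 10.3 and a short extra programming task, with no added infants or data. The drawback is that the primary result may look less secure than under the present check.

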## **11. Sample size and statistical power estimation**

The sample size estimate is based on our pilot study; the time of complete meconium evacuation was 1.4 days, 1.2 days, and 1.2 days earlier in the breast milk enema group than in the saline enema group at  $23 \text{ w} \leq \text{gestational age} < 28 \text{ w}$ ,  $28 \text{ w} \leq$

gestational age < 29 w, and 29 w  $\leq$  gestational age < 30 w, respectively. Given that  $\alpha = 0.05$ ,  $\beta = 0.2$ , standard deviation (SD) = 2, sampling ratio = 1 and taking a 20% drop rate into account, the required total sample size is 78, 108, and 108 premature infants in each gestational age, respectively. A website was used to calculate the sample size (<http://powerandsamplesize.com/Calculators/>).

| Gestational age               | Difference | $\alpha$ | $\beta$ | SD | Sample size | Loss of follow-up | Final sample size |
|-------------------------------|------------|----------|---------|----|-------------|-------------------|-------------------|
| 23W $\leq$ Gastinal age < 28W | 1.4d       | 0.05     | 0.2     | 2  | 64          | 20%               | 78                |
| 28W $\leq$ Gastinal age < 29W | 1.2d       | 0.05     | 0.2     | 2  | 88          | 20%               | 108               |
| 29W $\leq$ Gastinal age < 30W | 1.2d       | 0.05     | 0.2     | 2  | 88          | 20%               | 108               |

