We propose to recruit 78 super premature infants and 216 preterm infants from the Department of Neonatology, Shengjing Hospital of China Medical University. Recruitment will occur from June 2019 to September 2020 and will be conducted on-site. Leaflets with trial information will be displayed onsite in the waiting room of the neonatology department. A research assistant will ask each participant's guardian if they would be interested in having their babies participate and will be given sufficient time to make their decision. The guardian can contact the research assistant using the provided telephone number and undergo screening to enter the trial.

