#### **14.2 Analysis of Primary Outcomes**

The two primary outcomes include the time to achieve complete meconium evacuation and the time to complete enteral feeding. Outcomes are presented as median (Q1-Q3). The outcomes will be analyzed using an independent sample t-test or Mann–Whitney test. Meanwhile, a multiple linear regression model will be used to analyze the factors affecting primary outcomes, including gender, birth weight, history of a mother's disease, etc. For outcome differences between the treatment and control arms, the median difference and 95% confidence interval (CI) will be assessed using the Mann–Whitney U test and the Hodges–Lehmann method. The time to achieve complete meconium evacuation and full enteral feeding will be analyzed using Kaplan–Meier curves and log-rank tests. In the Kaplan–Meier analysis, the computation of the median time holds significant methodological importance.

Precisely, the median time to accomplish complete meconium evacuation and full enteral feeding are ascertained as the time point at which 50% of the study participants reach these predefined endpoints.

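### The allowance for 20% loss in Protocol section 11 is 2 infants short in each gestational-age group, so power per group is slightly below the stated 80%

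*Protocol*

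**What the plan says.** Protocol section 11 sizes each gestational-age group separately, from pilot data in which "the time of complete meconium evacuation was 1.4 days, 1.2 days, and 1.2 days earlier in the breast milk enema group" (groups 23 to <28, 28 to <29 and 29 to <30 weeks). The other inputs are α = 0.05, β = 0.2 and "standard deviation (SD) = 2, sampling ratio = 1 and taking a 20% drop rate into account". The table gives base totals of 64, 88 and 88, a loss of 20% in every row, and final totals of 78, 108 and 108. The text describes these as the requirement: "taking a 20% drop rate into account, the required total sample size is 78, 108, and 108 premature infants". No inflation formula is given.

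Section 4.2 carries the totals into the recruitment target: "We propose to recruit 78 super premature infants and 216 preterm infants", that is 294 infants.

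On testing, section 14.6 says "A two-sided $P < 0.05$ will be considered statistically significant", and section 14.2 says of the two primary outcomes that "The outcomes will be analyzed using an independent sample t-test or Mann–Whitney test".

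**The concern.** Each row of the table gives a required number, a loss and a final number, and the three should fit together. Taking 20% off the final number should leave at least the required number, and in all three rows it leaves fewer. The stated totals therefore do not deliver the stated β = 0.2 under the stated loss.

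What is at stake is the accuracy of the power statement for each gestational-age group. A non-significant result in one group would be read against a power that is slightly too high. The same totals also set the recruitment target in section 4.2.

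**Working it through.** **Inputs.** Differences 1.4, 1.2 and 1.2 days, SD 2 days, α = 0.05, power 80%, allocation 1:1, loss 20% (section 11). Two-sided testing (section 14.6).

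**1. Reproduce the base figures.** Normal approximation for two means: n per arm = 2 × [SD × (1.960 + 0.8416) / difference]².
- 1.4 days: 32.04 per arm, 64.07 in total. The table has 64 (32 per arm). Power at 64 is 79.96%, so rounding down costs about 0.04 points.
- 1.2 days: 43.60 per arm, rounded up to 44, 88 in total. The table has 88. Power at 88 is 80.4%.

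One-sided testing would give totals of 52 and 70, so the table was built on a two-sided test with this formula or one very close to it.

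**2. Inflate for 20% loss.** The final number must satisfy final × (1 − 0.20) ≥ base.

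| Base total | Base / 0.8 | Base × 1.2 | Base × 1.2, rounded up per arm | Stated |
|---|---|---|---|---|
| 64 | 80 | 76.8 (77) | 2 × 39 = 78 | 78 |
| 88 | 110 | 105.6 (106) | 2 × 53 = 106 | 108 |

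Division by 0.8 gives 80 + 110 + 110 = 300, against 78 + 108 + 108 = 294. Multiplying by 1.2 with rounding per arm gives 78 but not 108. Neither usual rule gives both.

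**3. What remains after the stated loss.** 78 × 0.8 = 62.4 and 108 × 0.8 = 86.4, below 64 and 88.

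**4. Power at those numbers.** Normal formula: power = Φ(difference / [SD × √(2/n per arm)] − 1.960).
- 62.4 infants (31.2 per arm): 1.4 / 0.5064 − 1.960 = 0.805, power 79.0%.
- 86.4 infants (43.2 per arm): 1.2 / 0.4303 − 1.960 = 0.829, power 79.6%.

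The noncentral t distribution gives 77.7% and 78.7%. Part of that gap is not due to the loss allowance: the t-test already has 78.7% at 64 infants and 79.5% at 88. In whole infants (62 and 86) the normal formula gives 78.7% and 79.4%.

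**5. Loss that the stated totals absorb.** 1 − 64/78 = 17.9% and 1 − 88/108 = 18.5%.

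**6. The overall comparison.** With 294 × 0.8 = 235.2 infants (117.6 per arm), a 1.2-day difference and SD 2: 1.2 / 0.2608 − 1.960 = 2.64, power about 99.6%.

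**The case against.** The best reply is that this hardly matters. By the formula behind the table, the shortfall after a full 20% loss is 0.4 to 1.0 points, and 20% is itself a planning guess. The withdrawal that section 15 anticipates comes after meconium evacuation and before full feeding. It would fall on the second primary outcome rather than on the one that section 11 powers. All of this stands, and it limits the point to a minor one. It does not make the table right, because section 11 applies the 20% to this very calculation and its columns still disagree.

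Several stronger readings are tempting, and the documents do not support them:
- A reader might infer that the youngest group needs 84 infants, by rounding 32.04 up to 33 per arm, dividing 66 by 0.8 and rounding up again. That stacks rounding steps to recover about 0.04 points. The table's own base of 64 leads to 80.
- A reader might infer lower power still from the Mann–Whitney test. Section 14.2 names the t-test as an alternative. The usual efficiency loss of the rank test applies to exactly normal data, and with skewed data the rank test can be the more efficient of the two.
- A reader might multiply the three powers together. No section requires success in all three groups.
- A reader might take 78 as proof that the base was multiplied by 1.2. The same rule gives 106, not 108, for the other groups, so the origin of the figures is not established.

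**Conclusion.** The point holds as a minor error in the stated sample size and power. The final totals are 2 infants short in each group (6 in 294) of what the table's own base figures and loss require. After 20% loss, power per group is about 79.0%, 79.6% and 79.6% by the formula that reproduces the base figures, and 77.7%, 78.7% and 78.7% by t-test. These figures assume the stated differences, SD 2, equal arms, two-sided α = 0.05 and equal loss in both arms.

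A reader might conclude that the trial is materially underpowered, but the figures do not show that. Section 14.2 describes the primary analysis without restricting it to a gestational-age group, and section 14.5 lists the three groups as subgroups. An overall comparison of about 235 infants has about 99.6% power for 1.2 days. Section 14.2 does not name a pooled or stratified test, so that figure is context for the comparison it appears to describe.

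**What to change.** No further enrolment is needed. In section 11, name the inflation rule and make one of two statements:
- 78/108/108 with 20% loss gives about 79–80% power per group by the normal formula (about 78–79% by t-test); or
- these totals retain the required 64/88/88 only if loss stays at or below about 17.9%, 18.5% and 18.5%.

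The section should also note that the base of 64 comes from rounding 32.04 per arm down to 32. Optionally, add the power of the overall comparison in section 14.2: about 99.6% for 1.2 days, SD 2, with about 235 infants.

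The cost is a text and table correction and a slightly less favourable power statement per group. The target in section 4.2 can stay as it is.
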